### Calibration of researchers

2.2

For calibration, an examiner, trained in dentistry and specializing in orthodontics, will evaluate 5 panoramic radiographies of inclined molars, which will not be part of the study. Two radiographic evaluations will be made (10 days apart) to check for intra-examiner agreement. The intraclass correlation coefficient (ICC) will be calculated to assess intra-examiner agreement ≥ 0.75 with respect to the measurement of lower molar inclination using pre-established radiographic measurements (described in item “Movement rate”). The evaluation will be performed with millimeter ruler + protractor and this researcher will not be involved in the treatment of patients. The same examiner will be trained to collect crevicular gingival fluid (CGF) for cytokine analysis and data collection for OHIP-14 to maximize reproducibility of evaluations.

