### Study variables

2.13

The primary variable of the study will be

Radiographic measurements to assess movement rate through tooth angulation vs time at baseline and the final of the treatment.

The secondary variables of the study will be:

Oral health-related quality of life (HRQoL) will be assessed using the OHIP-14 baseline questionnaire applied at baseline and 90 days after treatment.Assess pain during orthodontic verticalization movement using the Visual Analog Scale (VAS) at baseline 30, 60, and 90 days after mini-implant placementAssess the amount of painkillers ingested in the period to verify that this therapy is effective in reducing pain during baseline orthodontic movement, 3 and 7 days, 30, 60, and 90 days after mini-implant placement.evaluation of IL-6, IL-1β, IL-8, TNF-α and IL-10 cytokines by baseline (T0), 3 (T1) and 7 days (T2), and then only in T1 (on 30 and 60 days).

*Movement rate* - With the aid of a ruler (Morelli, Sorocaba, SP, Brazil) and a protractor (transparent Waleu 10290001), an initial panoramic radiography will be compared to a final panoramic radiography (on day 90th) to ascertain the amount (in degrees) of verticalization. By draw a mandibular line (where 1 end would be the lower posterior part of the right goniaco angle region and the other its corresponding left side) and the long axis of the tooth,^[45]^ forming an angle (the larger, the larger the inclination of the tooth). These measurements will be recorded in degrees in each patient's chart for further analysis.

*Pain during movement* - Will be assessed by applying the visual analog scale (VAS) with a 100 mm line, with both ends closed. One end has the indication “0” and the other “100” which means “no pain” and “unbearable pain” respectively. Marking instructions will always be given to the patient by the same operator. Each patient will be instructed to mark with a vertical stroke the point that best corresponds to the pain intensity at the moment of evaluation.^[46]^

*Rescue medication* - Another parameter analyzed will be the amount of analgesics ingested, as proposed by Bauer 2013.^[47]^ At the beginning of the research, a paracetamol (drug with purely analgesic effect^[48]^) card will be delivered to each patient. It should be stored until the end and its use will be released only in case of pain. At the end of the experiment, the number of pills will be evaluated as another parameter to measure pain. This data will be collected by an auxiliary.

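### The reader of the primary angle is accepted on a point-estimate ICC of 0.75 from five films, a weak screen that tests the single-film angle rather than the change between films

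*Protocol article*

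**What the plan says.** Section 2.2 (Calibration of researchers) describes the only check on the angle measurement that the article gives. One orthodontist "will evaluate 5 panoramic radiographies of inclined molars, which will not be part of the study". On repetition it says: "Two radiographic evaluations will be made (10 days apart) to check for intra-examiner agreement". On the standard: "The intraclass correlation coefficient (ICC) will be calculated to assess intra-examiner agreement ≥ 0.75", and this is "with respect to the measurement of lower molar inclination using pre-established radiographic measurements", with a pointer to the Movement rate item. The instrument and the examiner's independence are also fixed: "The evaluation will be performed with millimeter ruler + protractor and this researcher will not be involved in the treatment of patients".

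Section 2.13 (Study variables) names the primary variable: "Radiographic measurements to assess movement rate through tooth angulation vs time at baseline and the final of the treatment". Under Movement rate, one baseline panoramic film is compared with one day-90 film, and the difference in degrees is the amount of verticalization.

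The article gives no confidence interval or lower limit for the ICC, no tolerance in degrees, and no reliability for the change. It does not say how many times each trial film is read. That the calibrated examiner also reads the trial films is strongly implied by the pointer to Movement rate, but is not said outright.

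**The concern.** The rule has two weaknesses.

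- **Too few films for a point-estimate rule.** An ICC from five films is very imprecise. A rule that compares its point estimate with 0.75 passes some poor readers and rejects some good ones.
- **The tested quantity is not the outcome.** The ICC concerns inclination on a re-read of the same film, where differences between patients push the coefficient up. The outcome is a difference between two separate films. Each film brings its own reading error, and the patient-to-patient spread in level that helped the ICC drops out.

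Reading error adds to the variance of the primary outcome. With 17 patients per arm, that is precision the trial can ill afford to lose, and the calibration as written gives little assurance that the error is small.

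**Working it through.** **Inputs from the article:** n = 5 films, k = 2 readings per film, acceptance at ICC ≥ 0.75 (section 2.2); two films per patient, outcome = change in angle (section 2.13). The article gives no derivation for the five films or for 0.75, so there is no planned figure to reproduce.

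**Inputs assumed (not in the article):** SD of single angle readings across patients 8 to 10 degrees; SD of the true 90-day change 5 to 10 degrees; reading errors independent between films and between readings.

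**1. Confidence interval at the pass mark.** For two readings, F = (1 + ICC)/(1 - ICC) = 1.75/0.25 = 7.
- One-way ICC, df (4, 5). The 97.5% points are F(4,5) = 7.388 and F(5,4) = 9.364.
  - Lower: 7/7.388 = 0.9475, so (0.9475 - 1)/(0.9475 + 1) = -0.03.
  - Upper: 7 × 9.364 = 65.55, so 64.55/66.55 = 0.97.
- Two-way consistency ICC, df (4, 4), 97.5% point 9.605. Limits -0.16 and 0.97.
- With 30 films, the same observed 0.75 has limits 0.54 and 0.87.

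**2. Chance of passing.** For true ICC ρ, P(pass) = P(F ≥ 7(1 - ρ)/(1 + ρ)). At ρ = 0.50 the cut is 7 × 0.5/1.5 = 2.33; at ρ = 0.90 it is 7 × 0.1/1.9 = 0.37.

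| True ICC | Pass, 5 films (one-way / two-way) | Pass, 30 films |
|---|---|---|
| 0.50 | 0.19 / 0.22 | 0.01 |
| 0.60 | 0.28 / 0.30 | 0.07 |
| 0.70 | 0.40 / 0.42 | 0.28-0.29 |
| 0.90 | 0.82 / 0.82 | 0.996 |

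So with five films a reader with true ICC 0.90 fails about 18% of the time.

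**3. From the ICC to error in the change.** Error SD of one reading = SD × √(1 - ICC); error SD of a change from single readings = √2 times that. At ICC 0.75 these are 0.50 SD and 0.71 SD. For SD 8 to 10 degrees, the reading-error SD is 4 to 5 degrees and the error SD of the change 5.7 to 7.1 degrees. Averaging two readings per film brings the latter back to 4 to 5 degrees.

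**4. Outcome variance, single against duplicate reading.** With error variance e = SD²(1 - ICC) and true-change variance c, the ratio is (c + 2e)/(c + e).
- ICC 0.75, SD 8 (e = 16), true-change SD 10 (c = 100): 132/116 = 1.14.
- ICC 0.75, SD 10 (e = 25), true-change SD 5 (c = 25): 75/50 = 1.50.
- ICC 0.90, SD 8 (e = 6.4), c = 100: 112.8/106.4 = 1.06.
- ICC 0.90, SD 10 (e = 10), c = 25: 45/35 = 1.29.

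The excess is therefore 14-50% at ICC 0.75 and 6-29% at ICC 0.90.

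**5. What a lower-limit rule would demand.** For the lower 95% limit to reach 0.75, the observed ICC must be about 0.96-0.97 with 5 films, 0.89 with 20 and 0.87 with 30.

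**The case against.** - **Single reading is not stated.** A reader might infer from the silence that each trial film is read only once. The article does not say so, and a condensed article may leave replicate reading to the full protocol. This stands: the variance figures show what duplicate reading would gain over single reading, not a loss that the plan is known to incur.
- **The calibration is not useless.** A reader might conclude that five films cannot show reliability at all. That is too strong. The rule still rejects about 80% of readers with true ICC 0.50, and an observed ICC of about 0.96-0.97 would put the lower limit above 0.75. The fault lies in accepting a point estimate of 0.75.
- **The degree figures rest on assumptions.** The article gives no angle SD, and a reader exactly at 0.75 is the worst reader whom the rule intends to accept. If the examiner repeats the same landmark or axis error on both films of a patient, that part cancels in the change and √2 overstates the error. This also stands, and is why the ICC 0.90 figures are given alongside.
- **No bias, and not the main power problem.** Section 2.6 blinds the researcher who collects data and section 2.2 keeps the examiner out of treatment, so the documents give no ground for saying that reading error favours an arm. With 17 per arm and a standardized difference of 0.40 (one reading of the effect size in section 2.1), power in a two-sided 5% t-test is only about 20%. Cutting the variance by the factors above (1.14 to 1.50) would raise it to about 23-28%. The sample size is the larger problem, but it does not make a cheap gain in precision pointless.
- **It is only calibration.** Section 2.2 describes training before the trial, not a reliability study. But it is the only assurance the article offers for the primary measurement, and its numbers are fixed there.

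**Conclusion.** The concern holds as a weakness in the acceptance rule. It is worth correcting, and it does not threaten validity. The rule accepts the reader on a result compatible with anything from no reliability to near-perfect reliability, and it does not address error in the change. The interval and the pass probabilities follow from the article's own numbers under the usual normal model for the ICC. The variance excess of 14-50% (ICC 0.75) or 6-29% (ICC 0.90) depends in addition on the assumed SDs, on independent errors, and on trial films being read once, which the article leaves open. The consequence is lost precision and power.

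**What to change.** 1. Calibrate on about 30 archived panoramic films of inclined molars, read twice as now planned, and judge the lower 95% confidence limit of the ICC instead of the point estimate. With a limit of 0.75 this means an observed ICC of about 0.87. The rule is strict: a reader with true ICC 0.90 would meet it about 75% of the time (P(F(29, 29 or 30) ≥ F-cut × 0.1/1.9), F-cut = 1.87/0.13), so allow for retraining and a repeat.
2. State that the same blinded examiner reads every trial film twice, at least 10 days apart, in random order and without sight of the earlier reading. Mask the arm. Mask the time point only as far as possible: by section 2.10 the final film is taken before the mini-implant is removed, so the hardware will usually identify it.
3. Use the mean of the two readings as the primary measurement, and report the reading-error SD of the change in degrees.

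The cost is a few extra hours of reading by the existing examiner. It needs no extra patients or radiation, and trial films already taken can still be re-read. It assumes that about 30 suitable archived films are available.

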### Description of the sample

2.3

The sample will consist of patients aged 30 to 60 years, living in the city of São Paulo, Brazil, considered healthy after anamnesis and clinical evaluation, without periodontal disease, under orthodontic treatment or not, and needing recovery of the prosthetic space for oral rehabilitation, after lower molars loss and consequent inclination of adjacent elements. The procedures will not entail charges to patients, only to travel to the place of research (which, if necessary, may be supported by the researcher)

### Inclusion/exclusion criteria

2.4

Patients who are latex allergic, pregnant or breastfeeding, smokers, diabetics, patients undergoing head and neck radiotherapy, coagulation disorders requiring antibiotic prophylaxis for placement of mini-implants, with absolute indication for use of local anesthetics with vasoconstrictors, with decompensate systemic disease, with systemic or local infection (periodontitis or periodontal abscess), who have used anti-inflammatory drugs in the last 3 months before orthodontic treatment, will be excluded from the search.

Healthy patients (ASA I - negative medical history), systolic blood pressure less than 140 mm Hg and diastolic blood pressure less than 90 mm Hg, heart rate with 70 ± 20 beats/minute, requiring oral rehabilitation after loss of some posterior lower dental element (1st molar), with favorable periodontal condition to the installation of mini-implants and who agree and sign the informed consent, will be included.

Patients who may have any complications during the research period, such as: allergic reactions to any of the materials used, allergic reaction to paracetamol, have taken any other drug than the one available, etc. Or those who are in any way unable to attend any of the appointments on the scheduled dates (in all, will be 10 dates, within 3 months), change cities, or simply no longer wish to participate in the survey, will be automatically excluded, without any compromise or damage to it (with removal of the installed apparatus). They will still be advised not to go to other professionals to intervene or continue treatment. Patients will be assisted by researchers for all research problems.

Any questions during the research period should be informed to the researcher so that the researcher can take the appropriate measures (the latter should provide some form of personal contact).

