### Study blinding

2.6

Only 1 external research collaborator, with dental training, who will be responsible for the treatments (which will open the envelopes of randomization), will know which photobiomodulation treatment will be assigned to each patient. The identification of each group will be revealed by this collaborator to all involved only after statistical analysis of the data. Therefore, the researcher responsible for data collection and the statistician will be blinded to the treatments assigned to the groups. The patient will also be blind to the type of treatment performed, since the mini-implant placement treatment will be identical in both groups and the laser treatment for photobiomodulation will be simulated in the control group.

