### Orthodontic verticalization mechanic and placement of the mini-implant

2.11

At the first consultation, all patients will be clinically and radiographically evaluated, and a treatment plan will be drawn up. Given the need for molar verticalization, an orthodontic mini-implant (Morelli, Sorocaba, SP, Brazil) will be installed in the retromandibular region (Araújo, 2006). First there will be a local asepsis with 2% chlorhexidine solution (2% aqueous chlorhexidine - Rioquímica) and external asepsis with 0.2% chlorhexidine (0.2% aqueous chlorhexidine - Rioquímica). The site will be anesthetized with a carpule (quinelato), short gingival needle (Unoject - Nova DFL) and the anesthetic of choice will be Mepivacaine + 2% Epinephrine 1 ml (Mepiadre 2% 1: 100000 - Nova DFL). The anesthetic technique used will be the infiltrative (essentially local) at 3 points of the retromolar region (central, buccal and lingual). Once this is done, the region will be pre-drilled by about 4 mm with a spearhead coupled to a manual key (Morelli ). In order to have proper anchorage and primary stability, the dimensions of the mini-implant will be chosen based on panoramic radiography and the amount of cortical bone present in the region.^[42]^ Once the mini-implant has been selected (Morelli, Sorocaba, SP, Brazil), it will be locked into position using a kit-specific digital key (Morelli, Sorocaba, SP, Brazil). Being threaded clockwise until the intramucosal mini-implant is at the gingival level. A simple surgery, where there is no osseointegration of the mini-implant, being inserted only in the cortical bone, being therefore easy to remove, and can be activated (force application) immediately. After installation, a metallic orthodontic lingual button (Morelli, Sorocaba, SP, Brazil) will be glued to the molar mesial face to be verticalized. As the molar is verticalized, this lingual button may be retracted more distally so that the elastic always exerts the proper force (this will be evaluated at each patient return by the calibrated operator). For its installation, molar prophylaxis will be performed with a Robinson brush (Robinson straight CA - Microdont brush) and prophylactic paste (Herjos - Coltene), followed by water irrigation and drying. Once this is done, the dental surface will be conditioned with 37% phosphoric acid (Condac - FGM) for 45 seconds, followed by water irrigation for 15 seconds and subtle air drying from the triple syringe. Next, we have the application of single bond adhesive system (Adper Single Bond 2 - 3M Adhesive) and polymerization (Poly Wireless Curing - Kavo) for 5 seconds. The lingual button will be glued to the inclined molar mesial with orthodontic adhesive (Orthocem - FGM), and a small portion of it will be placed on the lingual button grid and, once it is in position, it will be light cured for 45 seconds. A gray chain elastomeric ligature (Morelli, Sorocaba, SP, Brazil) will attach the head of the mini-implant to the lingual button glued to the molar mesial. A light force of 150 g will be imposed (measured with a tensiometer - Morelli, Sorocaba, SP, Brazil)^[43,44]^ in all cases, regardless of tooth position. This chain elastic will be changed every 30 days for a period of 3 months. After 90 days of the experiment time, the mini-implants will be removed. This procedure involves local anesthesia with Mepivacaine + 2% Epinephrine 1 ml (Mepiadre 2% 1: 100000 - Nova DFL) and the mini-implant will be removed only with the digital key being turned counterclockwise. Since there is no osseointegration, its removal is simple and quick, requiring no incision or suture. Painkillers will be available if there is pain. Removal of the lingual button will be performed using bracket pliers (346R-Zatty Straight Bracket Orthodontic Pliers) and resin removal with high-speed diamond drill bits (FG – Fava flame diamond). After the trial period, for those patients who are interested will be offered the possibility to complete (if this 3 months of research has not been achieved) the full verticalization of this molar (ie the mini-implant and lingual button would not be removed after 90 days and changes of the elastic bandage would occur until the case was finalized), so that they could receive future oral rehabilitation (making it clear to the patient that they would no longer be part of the research, and that any charge resulting from this choice would not fit to the researcher).

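### The vasoconstrictor exclusion in section 2.4 is inverted: it bars patients who need the type of anaesthetic every participant receives, and should read contraindication

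*Protocol article*

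**What the plan says.** The first paragraph of section 2.4 (Inclusion/exclusion criteria) is a single list of patients who "will be excluded from the search". One item on it is patients "with absolute indication for use of local anesthetics with vasoconstrictors".

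Section 2.11 fixes the drug. For placement, "the anesthetic of choice will be Mepivacaine + 2% Epinephrine 1 ml (Mepiadre 2% 1: 100000 - Nova DFL". For removal after 90 days, "This procedure involves local anesthesia with Mepivacaine + 2% Epinephrine 1 ml". No vasoconstrictor-free alternative is named at either step. Section 2.11 also lets interested patients keep the implant after day 90 to complete treatment outside the research, in which case the day-90 removal does not take place.

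Section 2.6 (Study blinding) says that "the mini-implant placement treatment will be identical in both groups", so the anaesthetic at placement does not depend on the arm.

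Several other provisions bear on who can be enrolled. Section 2.4 requires "Healthy patients (ASA I - negative medical history"), systolic pressure below 140 mm Hg, diastolic pressure below 90 mm Hg and a heart rate of 70 ± 20 beats/minute, and it excludes decompensated systemic disease. Section 2.3 describes the sample as "considered healthy after anamnesis and clinical evaluation". Section 2.8 has an anamnesis that records medical history and medications.

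**The concern.** An exclusion criterion about a drug normally protects people who should not be given it. This one points the other way. The protocol plans a vasoconstrictor-containing anaesthetic for everyone, yet the people it excludes are those for whom such an anaesthetic is required, and the article gives no reason for excluding them.

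Two things follow if the text is applied literally. A suitable patient could be turned away, and a patient in whom a vasoconstrictor is absolutely contraindicated is not caught by the one criterion that mentions vasoconstrictors. A screener who applies the sensible rule instead departs from the written protocol. The stakes are eligibility and participant safety; the treatment comparison is not at issue.

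**Working it through.** No formula applies. The check is whether the eligibility rule and the procedure can both be right, and whether other text supplies the missing rule.

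**1. Direction of the rule.** The clause sits in the exclusion paragraph of section 2.4, not in the inclusion paragraph that follows. Meeting it therefore means not entering the trial.

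**2. What participants receive.** Epinephrine is a vasoconstrictor, so the drug in section 2.11 belongs to the class named in section 2.4. Placement is the same in both arms (section 2.6), so every participant is planned to receive it at least once.

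**3. The two readings against the procedure.**

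| Reading of the criterion | Who is kept out | Fits section 2.11? |
|---|---|---|
| Absolute indication (as printed) | Patients who need a vasoconstrictor anaesthetic | No: that is what the trial gives |
| Absolute contraindication | Patients who must not have one | Yes: it protects them from what the trial gives |

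If the printed word were deliberate, one would expect section 2.11 to specify an anaesthetic without vasoconstrictor. It specifies the opposite, twice. Contraindication is an inference, but it is the only reading that fits both a list of safety exclusions and the stated procedure.

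**4. Whether another provision states the rule.**

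- The ASA I requirement, the blood-pressure and heart-rate limits and the exclusion of decompensated disease narrow the field, but none mentions vasoconstrictors. Section 2.4 also lists diabetes and decompensated disease separately although ASA I is required, so the authors did not rely on ASA I alone.
- The health check in section 2.3 and the anamnesis in section 2.8 collect information, but the article attaches no vasoconstrictor rule to them. The one exclusion in section 2.4 framed as recent drug use concerns anti-inflammatory drugs in the preceding 3 months.
- As context only: "allergic reactions to any of the materials used" appears in section 2.4 as a complication arising during the research, so it acts after exposure and does not screen for it.

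The inverted clause is therefore the only eligibility rule in the article on vasoconstrictor use.

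**5. Planned exposure.** With 34 patients (section 2.1), the anaesthetic is planned on 34 × 1 = 34 occasions if every implant is kept and 34 × 2 = 68 if every implant is removed at day 90. With the 40 envelopes of section 2.5, the range is 40 to 80. These figures count planned use, not errors; the article gives nothing from which to count patients wrongly admitted or refused.

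**6. No dose conflict.** The wording in section 2.11 places 2% next to epinephrine, but the product label in the same phrase gives one strength for each of two ingredients. Mepivacaine 2% is 2 g/100 ml = 20 mg/ml. Epinephrine 1:100000 is 1,000 mg/100,000 ml = 0.01 mg/ml. The dose is clear, and nothing here rests on it.

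**The case against.** The best case on the other side is that this is a slip of language with little effect. The article reads as a translation, and the same sentence sends patients out of the search where it plainly means the research. Nothing suggests that the investigators chose to exclude people who need vasoconstrictors. To come to harm, a patient would have to be ASA I with a negative history, within the blood-pressure and heart-rate limits and clear on the anamnesis, yet still have an absolute contraindication; the article offers no example. The operative text may also be the ethics-approved protocol, which is not shown and may be correct.

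Most of this stands as a limit on size. The error is probably one of translation, the other criteria remove most unsuitable patients, and whether any screener works from the inverted wording cannot be known from the article.

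It does not make the rule right. The other criteria reduce the risk without stating the contraindication, and an obvious slip in a safety criterion still gives the wrong instruction to anyone who follows it. Nor does the allowance for a condensed article help: that covers what is left out, whereas this clause is present and says the reverse of what the procedure requires.

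**Conclusion.** The concern holds. The vasoconstrictor exclusion in section 2.4 is inverted relative to the anaesthetic in section 2.11, and no other text in the article supplies the correct rule. The error is one word. The practical risk is small, and the number of patients affected may be zero. Randomisation, power, endpoints and analysis are not touched.

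The conclusion assumes that contraindication was intended and that section 2.11 describes what will actually be given. Confidence is high about the wording; no safety consequence is demonstrated or claimed. It is a correction that should be made, but not one on which the validity of the trial depends.

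**What to change.** In section 2.4, replace *indication* with *contraindication* in the vasoconstrictor item, so that patients with an absolute contraindication to local anaesthetics with vasoconstrictors are excluded. Check the ethics-approved protocol and the screening form for the same clause: if they are already correct, only the article needs a correction; if not, amend them as well.

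The cost is one word. Sample size, visits, procedures and analysis do not change. Whoever makes the correction could also write mepivacaine 2% with epinephrine 1:100000 at both places in section 2.11, but that is clerical and the point does not depend on it.

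### As worded, section 2.4 advises patients who have been excluded or have withdrawn not to seek treatment elsewhere, with no time limit (a minor patient-welfare correction)

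*Protocol article*

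**What the plan says.** The third paragraph of section 2.4 (Inclusion/exclusion criteria) sets out who is removed from the study after it has started. It names patients with a complication, patients who took a drug other than the one supplied, patients who cannot attend a scheduled date, and those who "change cities, or simply no longer wish to participate in the survey". All of these "will be automatically excluded, without any compromise or damage to it (with removal of the installed apparatus").

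Two sentences close that paragraph. The first is "They will still be advised not to go to other professionals to intervene or continue treatment". The second is "Patients will be assisted by researchers for all research problems". The paragraph that follows opens with "Any questions during the research period should be informed to the researcher".

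Two other places bear on the point. Section 2.3 describes the patients as "needing recovery of the prosthetic space for oral rehabilitation", so they have a clinical need for the molar to be uprighted. Section 2.11 contains an offer to finish treatment: "After the trial period, for those patients who are interested will be offered the possibility to complete", which is explained by "ie the mini-implant and lingual button would not be removed after 90 days". That continuation lies outside the research, and the researcher does not bear its charges.

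**The concern.** A trial may reasonably ask participants not to have the study appliance adjusted elsewhere while they are being followed. That reason ends when the patient leaves and the appliance comes out. Here the advice is written for patients who have already left, and it covers continuing treatment as well as interfering with it.

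A patient who took it literally could have a partly moved molar, no appliance, and a recommendation against finding someone to finish the work. It fits worst for a patient who has moved away and may be out of the team's reach, and for one who has withdrawn and owes the study nothing further. What is at stake is patient welfare, not the validity of the results.

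**Working it through.** The plan gives no figure for this point, so the check is mainly one of reading.

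**1. Who is addressed.** The pronoun opening the sentence follows directly on the list of excluded patients, and that list is the only plural group available. Their apparatus has been installed and is removed on exclusion, so the advice reaches patients in whom the movement may already have begun.

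**2. When it applies.** The sentence has no time limit. The next paragraph does limit itself to the research period ("Any questions during the research period should be informed to the researcher"), so the authors stated such a limit where they wanted one. The word *still* also suggests advice that holds despite the exclusion, although in loosely translated text it may mean no more than *also*.

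**3. Whether anything else lifts it.**

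| Text | What it gives | Does it lift the advice? |
|---|---|---|
| Section 2.4, "Patients will be assisted by researchers for all research problems" | Help with study-related problems | No. It does not say that treatment can be finished or that care elsewhere is acceptable |
| Section 2.4, exclusion without compromise or damage | A general assurance | No. It points to benign intent but does not alter the advice |
| Section 2.11, completion offer | Finishing the uprighting after the trial period | Not for early leavers. It works by leaving the mini-implant and button in place past day 90, and theirs are already out |

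Section 2.11 does not expressly shut out early leavers. By its timing and mechanism, however, it fits patients who still have the appliance at day 90.

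**4. How many patients.** Inputs: 3 extra patients per group and a 20% drop-out rate (section 2.1), and 40 numbers in the draw (section 2.5).

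- Planned allowance: 3 × 2 = 6, and 6 / 40 = 0.15, or 15%.
- At the stated rate: 0.20 × 40 = 8.

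If use of another drug is counted as its own reason, section 2.4 gives five kinds of reason for exclusion: complication, other drug, missed date, move of city and withdrawal. For two of the five, the move and the withdrawal, advice to stay with the team makes little sense. The article gives no expected count for either.

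**The case against.** The strongest reply is that the literal reading is not the intended one. Advice against outside intervention makes most sense while an appliance is in the mouth. The following sentence switches to patients in general and promises the team's help, and the next paragraph concerns the research period. Together these could mean simply that study-related problems should come to the researchers. The English is unreliable throughout, so a finding that rests on a pronoun and one adverb is fragile. The same paragraph also promises exclusion without compromise or damage, which sits badly with a wish to keep patients from care.

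Much of this stands. A reader might infer that the trial means to keep leavers from other dentists, or that patients are in fact told this. The documents do not support either inference. The milder meaning is plausible, the consent form (Annex 1) is not shown, and the Methods record ethics approval and conduct under the Helsinki Declaration. A reader might also infer that 6 or 8 patients would be left untreated. Those figures are drop-out allowances, and harm would also require that a patient is given the advice in its unlimited sense, follows it, and receives no further care from the team. Nor does the point show that the article must set out referral or completion arrangements for early leavers. That is after-care detail which an article may leave to the full protocol.

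What the reply does not remove is the sentence itself. It is a stated instruction, not an omission. If the milder meaning was intended, the sentence is in the wrong place and lacks its limit, and the correction is the same.

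**Conclusion.** The point holds as a minor patient-welfare correction. Read as written, section 2.4 tells patients who have been excluded or have withdrawn, and whose apparatus has been removed, not to seek treatment elsewhere. It sets no end to that advice, and no other text in the article lifts it.

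Few patients would be affected: at most about the 6 to 8 of 40 that the plan allows for, and probably fewer, since the Discussion considers dropout unlikely. Sample size, error rates, estimates and conclusions are untouched. Removal of the apparatus on exclusion is not in dispute.

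The conclusion rests on two assumptions: that the pronoun refers to the patients just listed, and that the consent form, which could not be read, does not already correct the advice.

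**What to change.** Delete the sentence, or limit it to active participation. For example: *While in the trial, patients should not have the study appliance adjusted by other professionals.* In either case, make clear that patients who have been excluded or have withdrawn are free to seek care elsewhere. Check that the consent form says the same.

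The cost is an edit to the protocol and, if the form repeats the advice, to the consent wording. It adds no patients, visits or procedures. Referral, or an offer to finish treatment with the team, would be a courtesy at the investigators' discretion and is not part of this point.
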